# The addition of simvastatin administration to cold storage solution of explanted whole liver grafts for facing ischemia/reperfusion injury in an area with a low rate of deceased donation: a monocentric randomized controlled double-blinded phase 2 study

**DOI:** 10.1186/s12893-018-0455-7

**Published:** 2018-12-27

**Keywords:** Donor after brain death, Liver transplantation, Simvastatin, Ischemia/reperfusion injury

## Abstract

**Background:**

Liver transplantation is the best treatment for end-stage liver disease. The interruption of the blood supply to the donor liver during cold storage damages the liver, affecting how well the liver will function after transplant. The drug Simvastatin may help to protect donor livers against this damage and improve outcomes for transplant recipients. The aim of this study is to evaluate the benefits of treating the donor liver with Simvastatin compared with the standard transplant procedure.

**Patient and methods:**

We propose a prospective, double-blinded, randomized phase 2 study of 2 parallel groups of eligible adult patients. We will compare 3-month, 6-month, and 12-month graft survival after LT, in order to identify a significant relation between the two homogenous groups of LT patients. The two groups only differ by the Simvastatin or placebo administration regimen while following the same procedure, with identical surgical instruments, and medical and nursing skilled staff. To reach these goals, we determined that we needed to recruit 106 patients. This sample size achieves 90% power to detect a difference of 14.6% between the two groups survival using a one-sided binomial test.

**Discussion:**

This trial is designed to confirm the effectiveness of Simvastatin to protect healthy and steatotic livers undergoing cold storage and warm reperfusion before transplantation and to evaluate if the addition of Simvastatin translates into improved graft outcomes.

**Trial registration:**

ISRCTN27083228.

## Background

Liver transplantation (LT) is the treatment of choice for end-stage liver disease. Ischemia/reperfusion (I/R) injury during the conventional cold storage and preservation of donated livers is a key determinant of graft function after LT. Hypoxia and reperfusion activate innate mechanisms of inflammation that cause injury and underline delayed graft function. [1–3] I/R injury causes almost 10% of early organ failure and can lead to the higher incidence of both acute and chronic rejection. [4, 5] Simvastatin suppresses the inflammatory effect in vascular endothelial cells, thereby protecting the liver against I/R injury and its effects on grafts from extended-criteria donors. [6–9] Statins or HMG-CoA inhibitors were primarily designed to decrease cholesterol levels. However, they have also shown to have beneficial cholesterol-independent effects, such as up-regulating the expression of the vasoprotective transcription factor Kruppel-like factor 2 (KLF2) and consequently, its derived transcriptional programs. Simvastatin protected healthy and steatotic rat livers undergoing cold storage and warm reperfusion before transplantation. [10, 11]

While the issue of I/R injury after LT has been addressed several times and pathophysiology of this entity has been extensively investigated in the context of pre-clinical studies, the attempts to solve this clinical problem have been scarce and unstandardized. This proposal offers a more targeted method of stratifying the differences on the liver sinusoidal milieu. The differences will be obtained with neither a complex therapeutic approach of combining different pharmacologic strategies nor the usage of machine perfusion methods, but by the sole cost of a single drug/placebo administration. In this novel approach, the infusion of Simvastatin will be applied directly into the donor liver’s portal vein after donor hepatectomy. The clinical trial allows avoidance of systemic infusion, so the protocol could also be applied in cases of multiorgan deceased donor retrievals.

### Donor shortage

LT is the only life-saving therapy for most types of end-stage liver disease. In Italy, the overall rate of cadaver donation is 22.2 donors per million per year, and in some regions, like Sicily, the rate is 12.6 donors per million per year. In the past few years, IRCCS-ISMETT, a transplant hospital in Sicily, has been committed to counteracting this organ shortage. Over the years, the number of transplants has steadily increased thanks to marginal donors, living donors, and split LT. ISMETT has implemented techniques and strategies to most efficiently use valuable resources in order to maintain a high level of LT. From July 1999 till May 2014, we performed 902 LTs for adults: 755 (84%) were performed by using 601 whole livers (80%), 99 (13%) were living-related LTs, and 55 (7%) were split LTs. The one-year survival rate (cadaveric liver transplantation) is 85.4%. [12–14]

The shortage of organs led to the use of steatotic liver grafts from extended-criteria deceased brain donors (DBDs), even though these livers are more susceptible to I/R injury and have poorer outcomes than non-steatotic livers. Preclinical studies have demonstrated that the negative effects of I/R can be prevented by adding Simvastatin to the cold preservation solution shortly before procurement to protect both parenchymal and endothelial components of the liver after warm reperfusion.

The proposed project aims to be the first prospective randomized clinical trial to prove the efficacy of Simvastatin in preventing I/R injury and expand the donor pool.

### Purpose

The primary endpoint is to investigate the effect of intra-gastric Simvastatin administration using a nasogastric cannula in addition to cold-storage on 3-month, 6-month and 12-month graft survival after LT. As secondary endpoints, we will compare 3-month, 6-month and 12-month patient survival, hospitalization stays, and all transplant-related complications in terms of the multi-tier Clavien grading system after LT. This will allow us to identify a significant relation into two homogenous groups of liver transplanted patients, only differing for Simvastatin or non-administration regimen; using the same procedure, with identical surgical instruments, and medical and nursing skilled staff.

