### Outcomes

The primary outcome measure in this trial is postoperative graft survival after LT. The secondary outcomes of interest are patient survival, hospitalization stays, and all transplant-related complications in terms of the multi-tier Clavien grading system after LT. The grading system is used in order to identify a significant relation into two homogenous groups of liver transplanted patients, which only differ for Simvastatin or non-administration regimen utilizing the same procedure, with identical surgical instruments, and medical and nursing skilled staff. Baseline data on graft function and patient performance status will be collected immediately prior to discharge from the recovery unit (T0). Follow-up measures will be collected at three time points**:** 3-month (T1), 6-month (T2) and 12-month (T3)**,** after LT (see Fig. 1). All participants will be routinely evaluated with a post-reperfusion liver biopsy (sample), intensive care monitoring, daily laboratory and ultrasound examinations for the first week after the operation and when required during their hospital stay.

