### Sample size

We hypothesize that Simvastatin’s protective effects may occur in the liver during the harvesting procedure from the deceased donor and could significantly ameliorate post-LT outcomes. To reach the above-mentioned goals, we decided to recruit 106 patients. This sample size achieves 90% power to detect a difference of 14.6% between the two groups survival using a one-sided binomial test. The target significance level is 0.05. These results assume a null hypothesis that the proportion of the group with the standard procedure is 0.85.

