### Interim analysis

Two interim analyses of drug tolerance and efficacy will be performed 6 months after the trial enrollment starting, and when 75% of participants have been enrolled in the trial, respectively. The level of significance will maintain an overall *P* value of 0.05 and be calculated according to the O’Brien-Fleming stopping boundaries. [16]

The DSMB will be instituted as an independent group of experts that will advise the clinicians and the study investigators, without direct involvement in the conduct of the study, nor financial, proprietary, professional, or other interests that may affect impartial, independent decision-making. The ISMETT Director of the Department for the Treatment and Study of Abdominal Diseases and Abdominal, the ISMETT Medical and Scientific Director and the primary investigator (PI) will have primary responsibility for the DSMB formation and for identifying the DSMB Chair and the terms of membership for the entire duration of the study. The DSMB will deliberate processes, including event triggers that would call for an unscheduled review, stopping guidelines, unmasking (unblinding) and voting procedures prior to initiating any data review. ISMETT investigators will collect, assess, report, and manage solicited and spontaneously reported adverse events and other unintended effects of trial interventions or trial conduct.

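### Graft survival at 3, 6 and 12 months is the primary endpoint under one 0.05 level, and nothing says which time point, or what combination, decides success

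*Protocol article*

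**What the plan says.** The Purpose section of the protocol article defines the primary endpoint as the effect of simvastatin "in addition to cold-storage on 3-month, 6-month and 12-month graft survival after LT". The abstract (Patient and methods) says the same without ranking the times: "We will compare 3-month, 6-month, and 12-month graft survival after LT". The Outcomes section drops the time point: "The primary outcome measure in this trial is postoperative graft survival after LT". It then adds that "Follow-up measures will be collected at three time points", namely 3, 6 and 12 months.

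The Sample size section has one calculation: "This sample size achieves 90% power to detect a difference of 14.6% between the two groups survival using a one-sided binomial test". It states one level, "The target significance level is 0.05", and one control proportion, 0.85, and ties none of these figures to a time point. The only observed survival figure in the article is under Donor shortage: "The one-year survival rate (cadaveric liver transplantation) is 85.4" per cent. Error control is mentioned once more, under Interim analysis: "The level of significance will maintain an overall *P* value of 0.05 and be calculated according to the O’Brien-Fleming stopping boundaries". The Statistical analysis section plans chi-squared or Fisher tests for categorical variables.

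**The concern.** Three results sit under the primary label and one significance level serves them all. The article gives no lead time point, order of testing, division of the 0.05, requirement that all three succeed, or single time-to-event test. The trial therefore has no unique success criterion. A result that is significant at 3 months but not at 12, or the reverse, could be read either way, and the choice could be made after the data are seen.

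There is a second strain. The sample size was worked out for one comparison, and its figures look like one-year figures. Cumulative graft survival cannot be lower at 3 or 6 months than at 12 months, so the planned gain may be arithmetically out of reach at the earlier times that share the primary label.

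**Working it through.** **Inputs.** Total of 106, one-sided 0.05, 90% power, control 0.85 and difference 14.6 points (Sample size), so the alternative is 0.85 + 0.146 = 0.996. One-year survival of 85.4% (Donor shortage). Assumptions: 1:1 allocation, hence 53 per arm; 12-month survival of 0.85; and early survival as a range, since the article gives none.

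**1. The plan's own figure.** Two proportions, unpooled variance:

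n per arm = (z₀.₉₅ + z₀.₉₀)² × [p₁(1 − p₁) + p₂(1 − p₂)] / (p₂ − p₁)²

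= (1.645 + 1.282)² × (0.85 × 0.15 + 0.996 × 0.004) / 0.146² = 52.8, so 53 per arm and 106 in total.

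The stated size reproduces. It pays for one comparison at 0.05.

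**2. Which time point it fits.** 100 − 85.4 = 14.6, and 85.4% is close to 0.85. A pooled-variance calculation of 0.854 against 1.00 also gives 53 per arm. The one-year figure is the only source in the article that yields these values.

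**3. Room for the planned gain.** The largest possible gain at time t is 1 − S(t), where S(t) is control survival. It reaches 14.6 points only if S(t) ≤ 0.854.
- S = 0.90: at most 10 points
- S = 0.92: at most 8 points
- S = 0.95: at most 5 points

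**4. Error rate if any one time point sufficed.** Null trials were simulated with nested losses, 53 per arm and 400,000 runs. Each time point was tested one-sided at 0.05 with a pooled normal-theory test.

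| Assumed survival at 3 / 6 / 12 months | At least one false success |
|---|---|
| 0.87 / 0.86 / 0.85 | 6.8% |
| 0.90 / 0.88 / 0.85 | 8.5% |
| 0.92 / 0.89 / 0.85 | 9.6% |
| 0.95 / 0.90 / 0.85 | 11.2% |

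Three independent tests would give 1 − 0.95³ = 14.3%. The nested outcomes are strongly correlated, so that is only an upper reference. Over the same range of survival:
- Fisher whenever an expected count is below 5, normal-theory otherwise: about 6.5–7.2%
- Fisher throughout: about 4–5%, because a single 12-month Fisher test here runs at 2.9%
- Requiring all three time points to succeed: about 1–3%

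With normal-theory tests, 1.9% to 6.3% of null trials are significant early but not at 12 months.

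**5. Early power depends on the test.** With no losses at all on simvastatin, power at control survival of 0.90 and 0.92 is 91% and 81% with the normal-theory test, and 62% and 42% with Fisher.

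**6. Cost of keeping all three.** A Bonferroni split puts each test at 0.05/3, z = 2.128: (2.128 + 1.282)² × 0.1315 / 0.0213 = 71.7, so 72 per arm or 144 in total. The pooled-variance version gives 76 per arm, 152 in total.

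**The case against.** The strongest reply is that the article never states an any-of-three rule. Listing the times with an 'and' could mean that all must succeed, Outcomes names a single primary outcome collected at three visits, and one time-to-event analysis would also fit. Neither of those readings inflates the error rate. This stands: a reader might infer that the plan allows a claim from any one time point at 0.05, but the text only leaves that open.

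The size of the inflation also depends on the test. A reader might combine error rates of up to 11% with early power of 62% or 42%, but the first comes from normal-theory tests and the second from Fisher. With Fisher throughout, the any-of-three rate stays at about 4–5%. Under the switching rule, one reasonable reading of Statistical analysis, the low power remains but the error rate is about 6.5–7%. That section also does not say that the final tests are one-sided. With two-sided chi-squared tests at 0.05, false success in simvastatin's favour at any of the three times would be about 4.4–5.3%.

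The 12-month link is an inference, and the 85.4% might be patient survival. An earlier time point could be argued on biological grounds, since the Background ties ischemia/reperfusion injury to early organ failure. Both points stand as cautions, but the planning figures match nothing else in the article.

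Two replies do not stand. The O'Brien-Fleming boundary spreads 0.05 over successive looks, not over three endpoints within a look. Nor is this a detail to leave to an analysis plan: the primary time point defines the endpoint, and the article actively gives three.

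**Conclusion.** The endpoint is badly specified. Three time points are primary, one level and one set of planning figures support them, and no decision rule connects the two. That follows from the text alone.

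The numerical consequence is conditional. If any one time point sufficed, the one-sided false-positive rate would be about 7–11% with normal-theory tests, about 6.5–7% when switching to Fisher, and about 4–5% with Fisher throughout, given 53 per arm, 12-month survival of 0.85 and assumed 3-month survival of 0.87–0.95. The documents do not support saying that the plan runs at 11%, or that it adopts the any-of-three rule.

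That a 14.6-point gain is impossible at any earlier time where control survival exceeds 85.4% is arithmetic. Whether early control survival does exceed it is not stated. The sample size calculation itself is not in error.

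**What to change.** In the abstract (Patient and methods), Purpose and Outcomes, name 12-month graft survival as the single primary endpoint carrying the 0.05. Make 3- and 6-month graft survival secondary, reported with confidence intervals and not used for the efficacy claim. Twelve months is proposed because it is the time point that matches the planning figures, so 0.05 and 106 patients stay consistent with the plan.

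The cost is wording only: sample size, visits and data collection do not change. The downside is that no efficacy claim can rest on 3 or 6 months alone. Keeping all three primary with a Bonferroni split would instead need about 144 to 152 patients. Trial status reports inclusions since 30 June 2018, so the change should be made and dated before anyone deciding on it sees unblinded outcomes.

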## Methods

### Trial design

The trial will employ a randomized administration of a single oral dose of 80 mg of Simvastatin (Sandoz®, Holzkirchen, Germany) (Group 1) or placebo (Group 2) per adult cadaveric donor through a nasogastric tube 1 h before the organ procurement, to investigate the effect of these interventions on graft survival after LT.

### Setting

The trial will be conducted in the operating rooms of a private hospital in Palermo (ISMETT), Italy and in every external hospital where all of the eligible DBDs are located. ISMETT was developed specifically for transplantation through a partnership of the Sicilian regional government and the University of Pittsburgh Medical Center. It is the first hospital in Southern Italy certified by Joint Commission International for excellence in clinical practice and is one of the first hospitals in Italy to use an entirely computerized process. It includes laboratories for clinical chemistry, microbiology, immunology and pathology, as well as laboratories that are equipped to support research activities. Liver transplantation is at the core of ISMETT transplantation programs. The ISMETT Abdominal Surgery and Transplantation operational unit has a team of 6 expert attending physicians and 2 surgery fellows, who manages the selection and care of patients requiring LT both from cadaveric and living donor. In ISMETT there is close collaboration and daily interdisciplinary teamwork with colleagues from other disciplines at ISMETT, including hepatologists, critical care clinicians, radiologists, endoscopists, and researchers from Ri.MED Foundation. An intense daily collaboration is performed with nurses, physical and respiratory therapists. One skilled research nurse will be recruited for guaranteeing the correct schedule of outpatient visit examinations, patient appointments and maximize the adherence. Ri.MED investigator will coordinate the effective functioning of the data and safety monitoring board (DSMB), maintaining information reviewed, discussed and recorded with the strict confidentiality. In addition, she will ensure the correct data recording of retrieval procedures, patient enrolment and data analysis in agreement DSMB recommendations and respect of the entire study phases.

### Eligibility criteria

Participants will be deemed eligible for the trial if they are 1) patients (male and female) over 18 years of age, 2) deceased brain donors (male and female) over 18 years of age, 3) female patients who are of child-bearing potential must ensure effective methods of birth control during the first 6 months of study following the whole LT, 4) patients with end-stage liver disease or terminal cancer liver disease, and a suitable candidate are placed on waiting list for primary LT at IRCCS-ISMETT, 5) patients who underwent liver transplantation from deceased brain donors (not identical human leukocyte antigen - HLA) compatible in terms of blood group ABO, 6) patients who can understand the purpose and risks of the study, have been fully informed and given written informed consent, 7) patients who are unable to read and/or write, but are fully capable of understanding the oral proposal by the researcher (or the appointed representative) and have given oral informed consent that is testified in writing by an independent third person.

The following subjects will be excluded by donor population: 1) pregnant or breast-feeding donors, 2) donor with autoimmune disease or allergies to statins, 3) donors requiring ongoing dosing with a systemic immunosuppressive drug at time of harvesting procedures, 4) donors known to be human immunodeficiency virus (HIV) positive, 5) donors with malignancy or history of malignancy, except for non-metastatic basal or squamous cell carcinoma of the skin that has been treated successfully, 6) donors had previously received or is receiving an organ transplant.

The following subjects will be excluded by recipient population: 1) recipients with acute liver disease, 2) pediatric patients or pediatric donors, 3) patients undergoing liver re-transplantation, 4) patients undergoing split or living donor liver transplantation, 5) patients undergoing combined liver- or other solid (abdominal or thoracic) organ(s) transplantation, 6) patient who is participating or have been participated to another clinical trial/study and/or has consumed an experimental drug in the last 30 days, 7) any clinically relevant conditions that might affect study participation and/or study results, 8) patients with history of allergy or intolerance to statins, 9) patients with history of substance abuse, and/or psychiatric disorders or conditions that may invalidate communication due to their inability to understand the potential risks and benefits of the study, 10) patients greater than 65 years old.

### Interventions

Participants will be allocated to one of two groups (see Fig. 1): Group one will receive an organ procured in a DBD after preoperative administration of Simvastatin; group two will comprise the control group receiving no DBD intervention before the standard organ procurement in a DBD or after.

**Fig. 1 Fig1:**
[figure not shown]
Study flow diagram

#### Experimental treatment

Simvastatin tablets on the market will be pulverized and placed in capsules in order to then be emptied at the time of preparation of the suspension at the clinical site during the start of the cold phase of the collection. An Investigational Medicinal Product Dossier (IMPD) will be drawn up before the trial begins and the authorization of the National Competent Authority (NCA) has been granted. The drug will be administered in the deceased donor prior to the allograft procurement by using a nasogastric tube, and it will be subsequently transplanted into the recipient. Two Simvastatin 40 mg tablets (Sandoz®, Holzkirchen, Germany) will be pulverized and encapsulated in order to be emptied at the moment of the preparation into a hydro-alcoholic suspension at the clinical site during the start of the cold phase collection. The suspension will then be administered via an intragastric route using a nasogastric cannula one hour before vascular clamping in the DBD surgical liver procurement procedures. [15]

Criteria for discontinuing or modifying allocated interventions for a given trial participant will be defined after histologic examinations of back-table and post-reperfusion liver biopsies (Fig. 1). The therapeutic intervention will be applied to the DBD before transplantation, and for this reason, no strategies to improve adherence to intervention protocols, and any procedures for monitoring adherence will be implemented. No relevant concomitant care and interventions are prohibited during the trial.

